### HLS app prototype

2.2

The HLS app prototype for mobile device platform(s) (IOS/Android) is intended to be used in future HLS interventions directed at new firefighters. Using firefighters’ direct input, existing scientific literature, and reliable online resources, this HLS app titled “Surviving & Thriving” will be designed and developed to help firefighters implement and maintain lifestyle habits that optimize their health and functional performance. The app will promote the combination of balanced nutrition, regular physical activity, restorative sleep, positive social and family connections along with resilience/stress-reduction strategies, and the avoidance of tobacco, binge-drinking, and other toxic substances. In order to accomplish this goal, the app will provide a wide array of multi-domain content (i.e. physical activity, sleep, nutrition, resilience), deliver weekly motivational messages, promote the use of a habit tracker, and facilitate user-interaction through team missions. The content of the HLS app has been visually depicted in our “Surviving and Thriving” app logo (**Figure 1**).

**Figure 1 f1:**
[figure not shown]
*Surviving & Thriving* mobile application logo.

The final app prototype will include a total of three self-study levels in each HLS domain. Each level is comprised of 10 quests. These levels reflect career firefighter rankings (i.e. Lieutenant, Captain, Chief) and are represented with corresponding badges. Quests are comprised of educational content pertinent to each of the four designated lifestyle factors specifically tailored to the needs of career firefighters (**Figure 2**). The educational component is followed by a corresponding mechanical task that either promotes reinforcement of learned concepts or behavior change that can be recorded in the app’s habit tracker. This evidence-based content was created by the research study team based on information, audiovisual content, and validated assessment tools from various accredited online sources and peer-reviewed articles. To enhance user engagement, the HLS app also utilizes gamification mechanisms that allow users to create personalized firefighter avatars to journey through the three levels of quests and complete missions both individually and as teams of firefighters who can cross-motivate each other. Of note, alpha and pre-beta testing detailed in the following section, will utilize the MVP which is limited to the first level of quests. Operational individual components, namely the educational materials, onboarding survey and personalized journey, *surviving* and *thriving* point system, and gamification mechanisms (e.g. users’ avatar set-up, habit tracker, community and leaderboard, and missions) will then be assembled into a final viable prototype. Detailed wireframes will be made for all the educational material and gamification features by a UI/UX designer with the appropriate design software, Figma (Figma Inc., San Francisco, California USA) (**Figure 3**). The app development with all the necessary platforms and interfaces for both iOS and Android devices will be carried out by a contracted Managed IT Services provider. The app itself is an intervention tool and no identifiable data will be collected directly through the app.

**Figure 2 f2:**
[figure not shown]
*Surviving & Thriving* healthy lifestyle app content themes across 4 lifestyle domains, 3 levels, 10 quests per level.

**Figure 3 f3:**
[figure not shown]
Screenshots of the *Surviving and Thriving* app prototype **(A)** Homepage **(B)** Journey page **(C)** Quest Progress **(D)** Quest Introduction **(E)** Quest Completion.

#### Nutrition domain

2.2.1

The main objective of the Nutrition domain is to help firefighters integrate a healthy balanced diet into their daily living. The first level focuses on the fundamental principles of nutrition (i.e., what are macronutrients, how to make a balanced meal etc.). The second level addresses specific food categories (i.e., whole foods, olive oil, lean protein etc.) and how the user can best incorporate them into an overall healthy diet. The third level focuses on adopting healthy eating habits and behaviors (i.e., eating out, grocery shopping, frugality, commensality, etc.). Presented as an example of a HLS, the Mediterranean diet and lifestyle were previously encouraged in a nutritional intervention among Midwestern career firefighters in which many website resources have been reutilized (28, 29). Despite its cultural and geographic origins, the principles of the Mediterranean diet can be culturally translated and easily adapted in non-Mediterranean populations (30, 31). Furthermore, national firefighter surveys on dietary preferences showed that the Mediterranean diet consistently received highest favorability ratings (32, 33). Similar dietary patterns concerned with overall diet quality, such as the DASH and MIND diets, may also offer comparable health benefits in this population (34, 35). Additional resources included the “Nutrition Source” from the Harvard T.H. Chan School of Public Health (36), “Oldways” a non-profit organization dedicated to the dissemination of traditional cultural diets (37), and the National Institutes of Health (38).

#### Physical activity domain

2.2.2

The objective of the Physical Activity domain is to encourage regular physical activity and help firefighters fine-tune their workouts so that they are well prepared for the physical demands of their job. The first level familiarizes firefighters with the core principles of physical activity (i.e., benefits, motivation, safety) and introduces them to the concept of “functional fitness.” The second and third levels expand on the “The Big Eight Method”, a firefighter functional fitness training regimen for optimal firefighter performance and longevity. With over 400 YouTube videos, this program was devised to provide firefighters with the tools, knowledge and mindset on how to optimize performance, reduce injuries/line-of-duty deaths, and extend career longevity. Firefighters learn how to easily program daily and weekly workouts, prioritize recovery and rest, as well as firefighter-specific hydration and nutrition (39). Each level contains exercises on functional strength, core strength, cardiovascular capacity, and flexibility that firefighters should implement into their daily workout routine. In addition, this domain includes materials from the Physical Activity Guidelines for Americans (40), as well as the Centers for Disease Control and Prevention’s webpage on physical activity (41).

#### Sleep domain

2.2.3

The Sleep domain aims to impart knowledge and facilitate habitual sleep behaviors that can help firefighters, despite their irregular shift-work schedule, attain sufficient sleep quality and quantity and ward off fatigue. The first level revolves around the importance of sleep and the impact of insufficient sleep on firefighters. The second level focuses on how to implement good sleep hygiene. The third level focuses on tracking sleep, understanding sleep disorders, and effective ways to address them. The educational material within the sleep domain is based on the National Sleep Foundation’s online resources (42) and the Division of Sleep Medicine at Harvard Medical School (43), as well as other firefighter websites which offered a more firefighter-centered viewpoint on achieving better sleep.

#### Resilience domain

2.2.4

The goal of the Resilience domain is to help firefighters cultivate the necessary “mental skillset” to deal with adversity and thrive in both their career and personal lives. The first level serves as an introduction to stress and basic relaxation techniques to help counteract negative consequences of stress. The second level moves on to resilience and self-care practices (i.e., gratitude journal, relaxation techniques, mindfulness) and learning how to deal with cognitive distortions. The third level focuses on the negative emotions and mental health issues that often affect firefighters. The resilience domain includes content inspired by the American Psychological Association (44), the National Institutes of Mental Health (45), and the Center for Wellness and Health Promotion at Harvard University (46). These general-purpose resources were complemented with firefighter-specific content including fire experts’ testimonies and perspectives on resilience and mental health.

## Methods

3

### Alpha and pre-beta testing of the MVP

3.1

**Figure 4** shows the flowchart diagram of the HLS app *Surviving & Thriving* development and pilot study design. At this time, the first aim has already been carried out. The first stage of internal testing involved “alpha” testing, which was conducted by the research team (n=5-10) by simulating the firefighter user experience. Alpha testing was done to identify possible problems and development errors of the MVP before it is shared with users within the target population. The MVP included the full onboarding content, which consists of a validated short questionnaire for each of the four domains, personalized avatar set-up, goal-setting, and a tutorial of the app’s basic features. The research team and developers have refined the HLS app based on the feedback collected during alpha testing accordingly.

**Figure 4 f4:**
[figure not shown]
Flowchart diagram of the HLS app *Surviving & Thriving* development and pilot study design.

“Pre-beta” testing of the refined MVP involved our fire service expert panel associated with the research team (n=10-15). The participants were generally experienced firefighters or leaders at their fire departments. This was a more specific form of alpha testing because it was carried out by potential end-users or consumers of the app. However, given that the pre-beta users were affiliated with the research team, this form of testing is still considered a form of in-house acceptance testing by individuals who are aware and open that the product is under development. The purpose of pre-beta testing was to help improve its utility and functionality. The pre-beta participants were then asked to engage in a satisfaction survey and online interview to provide further feedback and suggestions on refining the content and usability of the newly developed app. This has allowed the research team to update the HLS app prototype before field testing the “pre-consumer” version.

### Usability testing (beta testing)

3.2

By partnering with two academies in the New England area (Connecticut and Stow, MA) we will have access to over a hundred new firefighters to recruit from for “beta” testing. We will recruit ~55 new firefighters from recently graduated academy classes and ask that they complete 14 days of usability or beta testing on their smartphones. Our proposal has been designed to ensure that it is open to all probationary firefighters regardless of race or gender. The link to download the app will be emailed to the participants after they consent to participate and all participants are expected to explore the functions of the app. Although creating an account for the app requires using a personal email, the research team will not access any of the participants’ private information from the app, including email addresses. The data collected from the app (i.e. time spent on the app, screen views, retention, etc.) will be processed according to appropriate de-identifiable security procedures.

As part of beta testing, focus groups and satisfaction surveys will be carried out. The focus groups will be moderated by at least one experienced member from the research team. Focus group discussion guides have been adapted from existing literature on similar smartphone app usability testing (47). The participants are asked to verbalize what they think about, are looking at, doing, and feeling throughout the process of using the HLS app. Thereafter, members of the research team will independently analyze qualitative focus group data by coding the transcripts using commercial software such as NVivo 10 (QSR International, Victoria, Australia) to organize, sort and structure the data until saturation is reached and no new themes emerge. Similarly, a satisfaction survey adapted from a validated questionnaire will be distributed to the beta testing and Focus Group participants (n=30) (48).

### Pilot study phase

3.3

This phase of the study aims to demonstrate that enrolled participants from the new firefighter study population can maintain adherence to the HLS app for at least 3-6 months. We will recruit ~50 new firefighters (a separate cohort from those enrolled in the beta testing) and monitor their app usage. App metrics such as session duration, screen views, and user retention within the app will provide insights into how users interact with the app over time. This cohort of new firefighters for the pilot study phase will also assess the HLS app’s ability to maintain/improve HLS parameters (HLS scores, physical fitness, mental health (trauma/depression) screeners). For the purposes of this pilot study, we will conduct a small single arm trial which aims to obtain preliminary evidence of the efficacy of a novel digital intervention and to collect qualitative feedback from a subgroup of target users. Changes in HLS parameters throughout the pilot testing will be evaluated with repeated measures of health metrics pre-and-post app usage among those participants that engaged in the HLS app for 3-6 months. Namely, participants will receive the same lifestyle and mental health questionnaires and fitness test at the two time points: before using the HLS app and at the subsequent follow-up (i.e. 3-6 months after). Both adherence and efficacy results will be adjusted for the potential influence of new firefighters’ demographic characteristics. Effect modification analysis will include fire crew, station and department cultures/policies (measured by the “Health Culture” score as mentioned below in 3.3.4.).

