Aim 2- Usability testing: Conduct beta testing of the HLS app prototype by fire academy graduates working as probationary firefighters among veteran firefighters in typical career fire service environments. This field pilot test includes collecting the users’ qualitative and quantitative feedback regarding user acceptance via focus groups and satisfaction surveys, respectively.

Aim 3- Pilot study: Assess the HLS app for its ability to maintain adherence to the HLS app content for at least 3-6 months and its effects on maintaining/improving HLS parameters (HLS scores, physical fitness, and behavioral health (trauma/depression) screeners) in US career firefighters.

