### Participant incentives

3.5

Aim 1 was conducted on a volunteer basis by the research team and fire service expert panel with no formal compensation for the alpha and pre-beta testing of the development phase. For Aim 2 on usability (beta testing) among 50 enrolled new firefighters, we will conduct Focus Groups via Cambridge Health Alliance (CHA) Google Meet (expected n=25) compensated with a gift card, and satisfaction surveys (expected n=30) compensated by a gift card to get additional “end-user” feedback. For Aim 3, ~50 new firefighters will be recruited for pilot testing and their app usage will be monitored if they have completed more than three months of use (expected n=50). Upon completion of the pilot phase, participants will be given an additional gift card for a follow-up collection of health measures to compare against their baseline values.

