In the pilot study phase, Aim 3, adherence to the HLS app will be measured continuously as the total number of engagements with the software by each participant over the 3 to 6-month pilot study. This outcome will be supported by other prespecified app-usage metrics facilitated by the Managed IT Services provider (i.e. app user information; sign-ins, quest completion rate for each level, frequency of habit tracker use, and number of missions initiated). The primary outcome for validating the efficacy of the HLS app among the new firefighters’ will be the changes in the HLS score, comparing the participants’ pre- and post- app-usage scores (10). Using a behavior change measure (i.e. HLS score) as a primary outcome is justified in an intervention of short duration (11). As secondary outcomes, we will evaluate changes in 1-min pushups and mental health parameters. In addition, we will examine whether the health culture in various fire service workplace environments, as measured by the Health Culture score, influences the intervention effect of the app on the primary and secondary outcomes.

Generalized linear models will be utilized to assess the effect of the proposed app intervention comparing pre and post HLS scores, mental health scores, and 1-min push-up capacity upon completion of 3-6 months of app usage. All models will have their assumptions verified, using analysis of the residuals and other diagnostic testing. Generalized linear modeling will be used to model changes over time after taking into consideration the specific variance-covariance structure of repeated measurements or using other statistical methods such as generalized estimating equations models. All models will be adjusted for demographic and working conditions and other potential confounders. Interaction terms will also be incorporated into the models to evaluate any potential effect modification by working conditions, cultures, and policies. Statistical significance for all analyses will be considered as a two-tailed *p*<0.05.

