We recognize that our study and app prototype have some potential limitations. First, a potential response bias is dependent on quest completion rates and overall evaluations of individual performance and progress, which greatly rely on what the user reports and/or uploads, which may not be congruent with their actual behavior. Second, participants will be aware of their participation in a pilot study of a lifestyle behavior change tool and the fact that they are under observation, our pilot study will probably be susceptible to performance bias and social desirability. Third, it can be argued that the pilot phase, which spans 3 to 6 months, may be too short to gauge whether the app-based intervention will have a significant impact on the health outcomes of professional firefighters, whose careers are usually decades-long. Regarding the technical features of the app itself, at this stage there is no option to integrate data from other mobile apps that estimate a range of cardiometabolic and other health parameters that the user may be already using. Also, we recognize that there is limited personalization since all users will have the same set of tasks that are required to complete the avatar’s journey. Nonetheless, the order of their weekly quests/tasks will be arranged based on their baseline goal setting.

Ultimately, our goal is to develop and test the usability and feasibility of a viable, user-friendly and engaging HLS app that will help new firefighters maintain and improve their training-derived health/fitness levels more effectively, as compared to those before engaging with the HLS app. Firefighters that engage regularly with the app are expected to demonstrate measurable and plausible changes in the HLS parameters covered by the app (nutrition, sleep, physical activity, resilience) in the desired direction. The current research will support the implementation of this app as the primary intervention strategy in a multi-center controlled trial in the US fire service. The proposed future randomized clinical trial would collect laboratory tests to study the potential effect of this digital intervention on chronic disease risk factors in addition to habitual lifestyle behaviors. Ultimately, by sustaining the academy/training-derived health benefits into the probationary firefighter period, we expect firefighters will be more likely to maintain good health habits throughout their careers and thus increase their career longevity.

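### The pilot's adherence aim uses a range (3-6 months) as a minimum, and its main measure, total engagements over a window of varying length, cannot show whether use was maintained

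*Protocol article*

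**What the plan says.** The adherence aim appears twice in the protocol article. In the Introduction, Aim 3 is to "Assess the HLS app for its ability to maintain adherence to the HLS app content for at least 3-6 months". Section 3.3 (Pilot study phase) is firmer and sets out to demonstrate that "enrolled participants from the new firefighter study population can maintain adherence to the HLS app for at least 3-6 months".

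Section 3.6 (Statistical analysis) states the main measure: adherence is "measured continuously as the total number of engagements with the software by each participant over the 3 to 6-month pilot study". It names supporting app-usage metrics, among them "sign-ins, quest completion rate for each level, frequency of habit tracker use, and number of missions initiated", and Section 3.3 adds session duration, screen views and user retention. No time point is attached to any of them.

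Two statements describe whose usage is followed. Section 3.3 says "We will recruit ~50 new firefighters (a separate cohort from those enrolled in the beta testing) and monitor their app usage", without a condition. Section 3.5 (Participant incentives) says of the same cohort that "their app usage will be monitored if they have completed more than three months of use", with 50 expected out of about 50 recruited.

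**The concern.** Two things are fixed badly.

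- **Duration.** The aim gives a range where a single minimum is needed. Three months and six months are different standards, and the text does not say which one applies.
- **Measure.** The headline quantity is a sum. It does not record when the engagements took place, and the window over which it is summed can differ twofold between participants. Whether use was maintained is a question about activity at a later time, which a sum cannot answer.

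The condition in Section 3.5 adds to this. Read literally, usage is monitored only in people who have already passed three months of use. A retention figure based on them would leave out those who stopped early, who are the people the aim most needs to count. Section 3.3 reads as though everyone is monitored, so the two sections should be reconciled.

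What is at stake is how readily the adherence result can be interpreted. This is the first goal stated for the pilot phase, and the article looks ahead to a larger trial of the same app. Section 3.3 also limits the pre-post comparison to participants who engaged for the same loosely stated period, so the wording matters beyond adherence alone.

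**Working it through.** The article gives no adherence rate, precision or success figure, so there is no stated number to reproduce. The checks below test whether the wording and the measure can decide the aim.

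**Inputs from the documents.** Cohort of about 50, single arm (Section 3.3); duration of 3-6 months (Aim 3, Section 3.3); total engagements as the main measure (Section 3.6). **Assumed, because the documents give none:** a constant monthly drop-off rate *d*.

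**1. Does the reading of the duration matter?** The share still using the app is (1 - *d*)^3 at 3 months and (1 - *d*)^6 at 6 months. Multiplying by 50 gives the counts.

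| Assumed monthly drop-off | 3 months | 6 months | Of 50 at 3 months | Of 50 at 6 months |
|---|---|---|---|---|
| 5% | 0.857 | 0.735 | 43 | 37 |
| 10% | 0.729 | 0.531 | 36 | 27 |
| 15% | 0.614 | 0.377 | 31 | 19 |
| 20% | 0.512 | 0.262 | 26 | 13 |
| 30% | 0.343 | 0.118 | 17 | 6 |

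At 10%, for example, 50 × 0.729 = 36.5 and 50 × 0.531 = 26.6. The gap is 6 participants at 5% drop-off, and at 20% the six-month count is about half the three-month count.

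**2. Can total engagements show maintenance?** Take a participant with *k* engagements a month.

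- Steady use observed for 3 months gives 3*k*, and the same steady use observed for 6 months gives 6*k*. The total doubles although the behaviour is identical.
- A participant with 3*k* engagements in month 1 and none afterwards also totals 3*k*, the same as the steady user observed for 3 months. One stopped and the other did not.

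The total therefore reflects both exposure time and intensity, and it cannot separate early heavy use from sustained use.

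**3. Could a proportion at a fixed time be estimated with about 50 people?** Exact (Clopper-Pearson) 95% intervals at n = 50:

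| Active | Proportion | Exact 95% CI |
|---|---|---|
| 20/50 | 40% | 26% to 55% |
| 25/50 | 50% | 36% to 64% |
| 32/50 | 64% | 49.2% to 77.1% |
| 33/50 | 66% | 51.2% to 78.8% |
| 40/50 | 80% | 66% to 90% |

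The intervals are wide but informative: those for 20/50 and 40/50 do not overlap.

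**4. What would a benchmark imply?** Purely as an example, take a 50% benchmark that the lower limit must exceed. The smallest passing count is 33/50, since 32/50 has a lower limit of 49.2%. The binomial probability of 33 or more out of 50 is 0.016 if true retention is 50%, 0.24 at 60%, 0.78 at 70% and 0.99 at 80%.

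**The case against.** The strongest reply is that this is a condensed article about a small pilot. Cut-offs, required shares and progression thresholds are commonly left to a full protocol or analysis plan, which is not shown. Aim 3 says assess, not demonstrate, and Section 3.3 speaks of preliminary evidence. The declared primary efficacy outcome is the change in HLS score. The passages can also be read together as a three-month floor with follow-up out to six months, and Section 3.5 leans that way. Finally, Sections 3.3 and 3.6 name retention and other usage metrics that could show persistence.

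Much of this stands. The absence of a pass mark is not in itself an error here. A reader might infer that the aim cannot fail, that any adherence result could be called a success, or that the sponsor could choose the standard after seeing the data. Each of these assumes that no threshold exists in documents not shown, so the article does not support them. A reader might also take the Discussion sentence "The current research will support the implementation of this app as the primary intervention strategy in a multi-center controlled trial" to mean that the next trial will go ahead whatever the adherence result. It is a general statement of purpose and sets no progression rule. It would likewise be too strong to say that an adherence result without a benchmark has no evidential value, since readers can judge reported usage for themselves. The two-tailed 0.05 rule would cover adjusted models of adherence, although it gives no test of whether adherence was maintained.

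Two things are not answered. An unseen plan may add detail, but it does not turn the range in the article into a single minimum. The three-month floor has to be inferred, partly from a monitoring condition in the incentives section. And the measure put first cannot answer the aim, while the metrics that could are not tied to a time.

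**Conclusion.** The point holds for the adherence part of Aim 3. The duration is stated as a range used as a minimum, and the main measure cannot show whether use was maintained. The supporting metrics are relevant but have no time point, and the two statements on whose usage is monitored do not agree.

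On size, with 10% monthly drop-off the two readings give about 36 and 27 of 50. Across drop-off rates of 5% to 30% the gap runs from 6 to 13 participants. These figures rest on an assumed constant drop-off and a cohort of exactly 50. They show how much the reading matters and do not forecast this pilot. The flaw in total engagements needs no assumed rate, because it follows from summing over time.

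This is an inexpensive improvement to how one pilot aim is specified. It does not show that the adherence aim was built so that it could not fail, and it does not affect the choice of HLS score change as the primary efficacy outcome.

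**What to change.** - In Sections 3.3 and 3.6, and in Aim 3, replace the range with one fixed time after each participant's start, for example month 3, with month 6 as secondary.
- Report the proportion of all enrolled participants with recorded activity in a set window at that time, with an exact 95% confidence interval. Sign-ins, quests, habit-tracker entries and missions are already planned and can supply it.
- Keep total engagements as a supporting description.
- Reconcile Section 3.5 with Section 3.3 so that app usage is tracked for everyone enrolled, not only for those past three months.
- Before enrolment, either name the sponsor's own benchmark for this proportion or reword the aim from demonstrating to estimating. Whether to set a benchmark, and at what level, is the sponsor's choice. The 50% used above is only an illustration.

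**Cost.** No extra participants or visits are needed. Usage logs must be extracted to a common point for every participant, and a month-6 figure requires logging to run that long for all of them. If a benchmark is named, the pilot can miss it: under the 50% example at n = 50, the chance of passing is about 78% if true retention is 70%, and 24% if it is 60%.
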